## Abstract

**Background:**

More than 10 % (approximately 60,000) of the adult population in Styria, a federal state in the south of Austria, is granted a residential stay in a health resort each year. The target group for these stays is the general population aged between 30 and 65 years with minor symptoms such as risk factors for cardio-metabolic diseases. Stays are financed by health insurance companies and last up to three weeks. The treatment during the stays consists of exercise and nutritional intervention as well as psychological support when needed. However, because of the absence of regional programmes linked with the residential stay, the sustainability of the interventions is questionable.

**Methods/Design:**

This prospective, controlled, multicentre, open-label study will compare two groups. Participants will be included in the study if they live in any of eight predefined Styrian regions and do not meet the minimal WHO physical activity guidelines. Those allocated to the intervention group will receive a voucher for 12 regional, standardised, sports club based exercise sessions. The members of the control group will come from different but matched Styrian regions and will receive an informative written brochure. The primary outcome will be the weekly level of health-enhancing physical activity, which will be objectively measured with an accelerometer and supplemented by an activity log book. Together with potential determinants of physical activity it will be assessed before, 10 weeks after and 12 months after the residential stay. Additionally, psychosocial determinants will be assessed by questionnaire and fitness (cardiorespiratory fitness, handgrip, balance) will be measured. In addition to the changes in measurable parameters, processes will be evaluated to learn about the facilitators and barriers of the implementation of the programme.

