### Study objectives

The primary outcome of this study will be the weekly level of accelerometer-determined health-enhancing physical activity, measured as minutes of moderate- to vigorous-intensity physical activity (MVPA) [12, 13]. The particular research questions are: 1) How many of the eligible people in the intervention group will participate in the regional, standardised, sports club based exercise programmes after the residential stay? 2) Are those who participate in the exercise programmes more likely to increase their physical activity behaviour than those who do not participate in the exercise programmes?

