### Sample size calculation

For the sample size calculation, the difference in minutes of MVPA measured in bouts ≥10 min is considered as a suitable parameter for health-enhancing physical activity [16]. According to several studies, MVPA is an appropriate parameter for that purpose [17, 18]. Jung et al. [16] evaluated the changes in MVPA after a supervised exercise intervention in a similar cohort (male and females, aged 51(10)) years suffering from prediabetes). After the intervention, MVPA was changed by 44.5 (72.2) minutes. Due to the fact that the intervention-induced changes in our study are supposed to be similar, we considered the changes in MVPA of the above-mentioned study to calculate the sample size in our study.

Given a clinically relevant difference of 44.5 min of MVPA between the intervention and control groups, a standard deviation of 72.2 MVPA of the differences and a two-sided significance level of 0.05, a sample size of *n* = 42 per group is needed to reach a statistical power of 80 %. Since drop-outs and those lost to follow-up may have an inestimable effect on the assumed standard deviation of the differences, the sample size will be increased to *n* = 48 persons per group. Expected value μ1 (intervention) = 84.1 MVPA, μ2 (control) = 39.6 MVPA. Calculations were undertaken via: http://www.clinical-trials.de/de/Werkzeuge/werkzeuge.html

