### Measurements

All study participants will be evaluated at two or three points in time (see Table 2).

**Table 2 Tab2:** Time schedule for the different measurements

	Baseline	Baseline fitness^a^	Follow up1^b^	Follow up2^c^
	PA & mediators		PA & mediators	PA & mediators and fitness
Physical activity (accelerometer, log book)	✓		✓	✓
Questionnaire	✓		✓	✓
Anthropometry		✓		✓
Cardiovascular fitness (bicycle ergometer test)		✓		✓
Physical function (6MWT, handgrip, balance)		✓		✓
Blood chemistry – laboratory		✓		✓
Medication		✓		✓

^a^directly after the stay at a health resort

^b^= 10 weeks after the beginning of the stay in the health resort

^c^= 12 months after the beginning of the stay in the health resort

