Physical activity will be objectively measured using an accelerometer (GENEActiv) together with a physical activity log book before the residential stay (T1), 10 weeks after the first day at the health resort (T2) and 12 months after the first day at the heath resort (T3). Participants will be instructed to wear the accelerometer during seven complete and consecutive days, 24 h each day. At the same time, a log book should be filled in detailing walking and cycling for transport, walking and cycling during leisure time and strength training. At the same time points, participants will be asked to fill in the Office in Motion Questionnaire [20].All study participants (from the intervention and the control groups) will be encouraged to participate in an ergometer test, three functional fitness tests and some laboratory tests. Cardiovascular fitness will be tested with a bicycle ergometer to exhaustion [21, 22]. In general, subjects should reach maximum exercise capacity in 8 to 12 min [23]. To ensure that the ergometer test protocols can be compared, all participants will have to perform the same test protocol, which consists of a 35-watt initial loading increment for 2 min. Subsequently, the work load will be increased by 10 watts every minute. Work capacity will be measured in watts. Maximum heart rate and Borg-RPE will be documented as parameters for exhaustion [24].Physical function will be evaluated with the 6-Minute Walk Test [25]. Participants will be encouraged to walk a maximum possible distance within 6 min, during which modifying the speed will be tolerated. Muscle strength will be measured using a handgrip dynamometer (Jamar hydraulic hand dynamometer J00105) [26] and balance will be tested using the one-leg stand [27].Quality of life will be assessed by the World Health Organisation Quality of Life WHOQOL-BREF scale [28]. Psychological mediators such as motivation [29], satisfaction with life [30], satisfaction with the built environment [5], positive and negative effects [31], self-efficacy [32], social support [33] and enjoyment of physical activity (single item) will be determined via questionnaire. Country of birth and education level will also be recorded.As anthropometric measurements, body weight, body height and abdominal girth will be evaluated.Laboratory parameters, including glucose, high density lipoprotein, low density lipoprotein, triglyceride, creatinine, sodium, potassium, calcium, chloride, phosphate, bicarbonate, GGT, GOT, GPT, BNP, NT-proBNP and HbA1c, will be recorded, and medication will be derived from the patient’s chart.

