### Statistical analyses

All the statistical analyses will be performed with IBM® SPSS® Statistics for Windows, Version 20 (IBM Corp., Armonk, NY, U.S.). P-values <0.05 will be considered to be statistically significant, and all tests will be two-sided. Data exploration using descriptive statistical analysis and inferential statistics will be performed. The sample data will be carried out by frequencies or percentages (categorical variables), means and standard deviations (continuous variables) and graphics. T-tests and chi-square tests will be used to compare the groups. If a normal distribution is not met, non-parametric tests will be applied. Analysis of covariance (ANCOVA) (comparing parameters after the intervention and after the follow-ups) between the intervention and control groups will be adjusted for the baseline values as the covariate analysis is performed.

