The second physical activity measurement will be quite soon (10 weeks after the first day at the health resort) after the residential stay and has been discussed at depth within the study group. Follow Up1 will only consist of physical activity measurements and the assessment of psychological mediators. The reason for this is that we are interested in whether short-term changes in physical activity patterns are possible within a short period of time. This information will also be interesting for the 12-months follow-up, because, compared to Follow Up1, the weekly amount of health-enhancing physical activity might have declined, but it should still have increased compared to the baseline level.

In summary, linking the health sector with the sports sector enables the access to community-based structures to increase the weekly amount of health-enhancing physical activity.

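### The primary outcome is not tied to one MVPA metric or one visit, and the follow-up dates in the abstract and the body disagree by 1 to 3 weeks

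*Protocol article*

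**What the plan says.** **Metric.** The Study objectives section gives the primary outcome as the weekly accelerometer level, "measured as minutes of moderate- to vigorous-intensity physical activity (MVPA"), and stops there: no bout length and no visit. The Sample size calculation section narrows the quantity: "the difference in minutes of MVPA measured in bouts ≥10 min is considered as a suitable parameter". Its planned difference of 44.5 min, SD of 72.2 and 42 per group (raised to 48) all refer to that bouted quantity. It names no visit either.

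**Testing.** The Statistical analyses section describes baseline-adjusted ANCOVA between the groups after the intervention and after the follow-ups, under one general rule: "P-values <0.05 will be considered to be statistically significant, and all tests will be two-sided". No comparison is ranked above another.

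**Dates.** The abstract says of the primary outcome that "it will be assessed before, 10 weeks after and 12 months after the residential stay". The Table 2 footnotes put the early visit "10 weeks after the beginning of the stay in the health resort" and the late one "12 months after the beginning of the stay in the health resort". The Measurements text agrees with Table 2 ("10 weeks after the first day at the health resort (T2")), and so does the Discussion for the early visit: "The second physical activity measurement will be quite soon (10 weeks after the first day at the health resort) after the residential stay".

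**Programme.** The Intervention section offers 12 free sessions, two a week, available directly after the stay. Scheduling the start during the stay is only the ideal. The sub-group section counts attendance over 12 months. The Background gives stays of at least one week, mostly up to three.

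**The concern.** A primary outcome needs one variable at one time. Here the variable is stated with a bout rule in one section and without it in another, and two follow-up visits have equal standing. After the data are in, a positive result at either visit could be reported as the primary result, with nothing in the text to contradict it.

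The two visits do not answer the same question. The trial's rationale is that the effects of a residential stay are not sustained. The Discussion presents the early visit as a look at short-term change and allows that activity may have fallen by 12 months. The choice of visit could therefore decide the conclusion.

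The date conflict adds to this. Whether the early visit falls after the free sessions or during them depends partly on which reference day is used.

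**Working it through.** **1. The plan's own sample size.** Inputs from the Sample size calculation section: difference 44.5, SD 72.2, two-sided alpha 0.05, power 80 %.

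n per group = 2 × (1.960 + 0.842)² × (72.2 / 44.5)² = 2 × 7.85 × 2.632 = 41.3, rounded up to 42.

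The stated figure is reproduced (the t-based calculation gives 42.3). It is a calculation for one comparison at 0.05, on bouted MVPA. The document gives no mean or SD for MVPA without the bout rule, so 80 % power has no stated basis for that version.

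**2. Two visits, each tested at 0.05.** The chance of at least one false positive is 1 − P(|Z₁| ≤ 1.96 and |Z₂| ≤ 1.96). The document gives no correlation between the two test statistics, so a range is assumed.

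| Assumed correlation | At least one false positive |
|---|---|
| 0 (independent) | 1 − 0.95² = 9.75 % |
| 0.3 | 9.5 % |
| 0.5 | 9.1 % |
| 0.7 | 8.3 % |
| 0.9 | 7.1 % |

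**3. Cost of keeping both visits as primary.** With Bonferroni, alpha is 0.05 / 2 = 0.025 per visit.

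n per group = 2 × (2.241 + 0.842)² × 2.632 = 50.03, rounded up to 51. Power at 48 per group is 77 %. The planned size does not cover two primary tests at 80 % power.

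**4. Gap between programme and early visit.** Twelve sessions at two a week take 12 / 2 = 6 weeks. Counted from the first day of the stay, the programme ends at week: stay + start delay + 12 / (sessions per week). With no delay and full attendance:

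| Stay | Programme ends (week from day 1) | Gap if visit is 10 weeks from day 1 | Gap if visit is 10 weeks from end of stay |
|---|---|---|---|
| 1 week | 1 + 6 = 7 | 3 weeks | 10 − 6 = 4 weeks |
| 2 weeks | 2 + 6 = 8 | 2 weeks | 4 weeks |
| 3 weeks | 3 + 6 = 9 | 1 week | 4 weeks |

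After a 3-week stay and under the first-day date, the visit falls inside the programme if the start is delayed by more than 1 week. With no delay, it does so if attendance is below 12 / (10 − 3) = 1.7 sessions a week. After a 1-week stay the corresponding limits are a delay of more than 3 weeks or attendance below 12 / (10 − 1) = 1.3 a week. Under the abstract's date they are 4 weeks and 12 / 10 = 1.2 a week for any stay.

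**The case against.** **Only one metric may be intended.** Both sections speak of health-enhancing physical activity, so the sample size section can be read as supplying the bout rule that the objectives omit. This stands in part. A reader might infer four versions of the primary result (two visits by two metrics) and an error rate well above 10 %. The text does not support that: no second metric is declared, and any four-test figure needs further assumed correlations between metrics. What remains is one definition left unreconciled between two sections.

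**Multiplicity rules may sit in an analysis plan that is not shown.** That is fair for adjustment procedures. Which visit and which variable are primary belongs in the statement of the primary outcome, and this document leaves both open.

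**The early visit has a stated short-term role.** The Discussion says so, which makes it less likely that this visit would be presented as evidence of sustained change. It still does not name the 12-month visit as primary.

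**Overlap with the programme is not the planned case.** Correct: with an immediate start and full attendance the sessions end by week 9 at the latest. A reader might go further and argue that two sessions with at least 40 min of aerobic work each (80 min) exceed the planned 44.5 min, so that the sessions alone could produce the effect. That sets one full attender's minutes against a mean difference between arms. For sessions alone to yield 44.5 min, about 44.5 / 80 = 56 % of the intervention group would have to attend both sessions in the measurement week without giving up other activity. The document gives no uptake figure. Attendance is also part of the intended mechanism, so stripping session minutes out of the early measurement would remove intended effect in one arm only and bias the comparison.

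**The date conflict is small.** Only the abstract differs from the body, and 1 to 3 weeks matter little at 12 months. At the early visit they change the gap after a 3-week stay from 4 weeks to 1.

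**Conclusion.** The point holds in this form: the primary outcome is not fixed to one quantity at one time, and the visit dates contradict each other. With two visits and no hierarchy, the false-positive rate for the primary claim is about 8.3 to 9.5 % for assumed correlations of 0.7 to 0.3, and 9.75 % under independence, instead of 5 %. The stated power is tied to the bouted metric alone.

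Measurement during the voucher programme is possible for late starters and irregular attenders, most easily after a 3-week stay under the first-day date. How many participants this would affect cannot be derived from the document.

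This should be changed. It does not invalidate the design, and the sample size arithmetic itself is sound for the single comparison it describes.

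**What to change.** - In Study objectives, name one primary endpoint: weekly accelerometer MVPA in bouts of at least 10 min, which is the sizing metric, at the 12-month visit, which matches the sustainability rationale. The visit is a choice, but one has to be made.
- Make the 10-week visit and MVPA without the bout rule secondary.
- Reconcile the reference day for both follow-ups across the abstract, Table 2 and the Measurements text, and for the early visit in the Discussion.

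This keeps alpha at 0.05 and leaves the calculation at 42 (48) per group, provided that the authors state that the 44.5 min difference is meant to apply at 12 months. The cost is wording. The downside is that the 10-week result can no longer carry the primary claim.

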**Discussion:**

It is known that during the residential stay, participants are receptive to new opportunities supporting health behaviour change, but that these measures are not sustained after discharge. The structured cooperation between the health sector that has to inform the participants and the sports sector that provides the wide network of standardised programmes is the strength of the study, but at the same time a challenge.

**Trial registration:**

ClinicalTrials.gov (Identifier: NCT02552134; date of registration: 15 September 2015)

## Background

Physical activity is an important predictor for health. According to the national and international guidelines, a minimum of 150 min of aerobic moderate-intensity physical activity or ≥75 min of vigorous-intensity physical activity, or an equal combination of both, is needed to gain substantial health benefits. In addition to aerobic activities, muscle-strengthening activities that involve all major muscle groups should be performed regularly, at least twice a week [1–3].

In Austria, only a minority of the adult population meet the physical activity guidelines [4, 5].

In Styria, a federal state of Austria, there is a population of 597,033 adults within the age range 30 to 65 years [6]. Out of these, about 60,000 persons are assigned to attend a residential stay at a health resort each year. The approval and payment for these stays is the responsibility of health insurance companies. The target group for these stays at health resorts is people who are basically healthy but show one or more health risk factors. The stays last at least one week, but most last up to three weeks. During the stays, comprehensive lifestyle interventions are provided taking physical activity, nutrition and mental health into account. The stays at the health resorts are different to stationary rehabilitation, where a disease-related treatment is obligatory. However, most of the stationary interventions – preventive as well as rehabilitative – lack sustainability [7]. As a result, the major problem is the missing link between the health resorts and – in the case of physical activity – regional health-enhancing physical activity programmes run by trained personnel [8].

Based on experience in a previous nationwide feasibility study [9, 10], a working group was established representing health insurance companies, national sports umbrella organisations and sports science professionals in the federal state of Styria. The working group established the so-called “HEPA-Styria” (**H**ealth-**E**nhancing **P**hysical **A**ctivity) project linking the health and sports sectors [11]. The project focuses on two fields of activity: 1) during a residential stay at a health resort, the provision of gateways for regional HEPA programmes by the establishment of minimal counselling; and 2) the organisation of regional, standardised, sports club based exercise programmes. As a result of this intervention, it is aimed that people who participate in the regional exercise programmes will be more likely to increase their health-enhancing physical activity than those who do not participate in the exercise programmes. Additionally, determinants of regular physical activity, as well as selected health outcomes, are expected to improve within the intervention group.

## Methods/Design

### Overview

The proposed study is designed as a prospective, controlled, multicentric open-label study that will take place in the federal state of Styria, Austria. Austrian health resorts (*n* = 149) who accommodate patients from Styria will be involved. Based on the communities people come from, the study participants will be divided into an intervention group and a control group. Eight different communities in the federal state of Styria have been selected. Four communities will provide regional, standardised, sports club based exercise programmes and four matched communities will not offer these programmes in the near future. In short, the process will be as follows. People from the eight communities will be approached before the residential stay and asked whether they agree to fill in a questionnaire and participate in a seven-day physical activity measurement programme. Those who agree and do not meet the WHO physical activity guidelines will be included in the study [3]. During the residential stay, members of the intervention group will receive information about the regional, standardised, sports club based exercise programmes in their close living environment. Members of the control group will receive a brochure about physical activity.

The study was approved by the local ethical committee (University of Graz, EK-NR 86-2014/15) and will be conducted according to the principles of the Declaration of Helsinki. Furthermore, the protocol was registered at ClinicalTrials.gov (identifier: NCT02552134).

### Study objectives

The primary outcome of this study will be the weekly level of accelerometer-determined health-enhancing physical activity, measured as minutes of moderate- to vigorous-intensity physical activity (MVPA) [12, 13]. The particular research questions are: 1) How many of the eligible people in the intervention group will participate in the regional, standardised, sports club based exercise programmes after the residential stay? 2) Are those who participate in the exercise programmes more likely to increase their physical activity behaviour than those who do not participate in the exercise programmes?

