### Intervention

During the residential stay in the health resort, members of the intervention group who do not meet the physical activity guidelines based on the accelerometer data will receive a so-called “starter package”. During the stay at the health resort, people who took part in the prior physical activity measurement programme will be informed about the regional programmes if they do not meet the physical activity guidelines.

This starter package will include information about the project, an informed consent form, as well as a voucher for 12 regional, standardised, sports club based exercise sessions which can be attended immediately after the stay. The costs for these 12 sessions will be covered by the project funds so that participants need not pay any fee. Ideally, the beginning of the regional, standardised, exercise programme should be scheduled during the residential stay. “Standardised” means that the instructors will receive an obligatory 18-h training programme, and the sessions will have a defined structure with the following quality criteria [14]:Number of exercise sessions per week: two sessions.Duration of each single session: 90 min.Maximum number of people in a training group: 12 people.Cardiovascular exercise during a single session: ≥40 min of moderate- to vigorous-intensity aerobic activities.Muscle-strengthening activities during one session: ≥30 min; ≥2 sets of ≥6 different muscle-strengthening activities.Coordination and flexibility: will not be performed as a distinct part but it will be integrated in the cardiovascular and muscle-strengthening sections of the programme.Feedback on individual physical activity goals: as a supplement to the standardised exercise programme, individual “physical activity homework” will be prescribed to ensure that the physical activity recommendations can be realised. Furthermore, participants will be encouraged to support each other by identifying helpful behaviour change strategies and applying social support. Ten minutes will be reserved for this at the beginning and end of each session.

The advanced job training will include lectures and a manual with 12 different predefined sessions. Furthermore, health aspects of physical activity will be introduced, as well as extended communications training.

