### Analysis of sub-groups

At the 12-months follow-up, the intervention group will be divided into sub-groups for further analysis:Sub-group I: participants who attended ≥75 % of the 12 exercise sessions of the standardised programme during the last 12 months.Sub-group II: participants who attended ≥25 % and <75 % of the 12 exercise sessions of the standardised programme during the last 12 months.Participants who did not attend 25 % of the 12 exercise sessions of the standardised programme.

The sub-group analysis is necessary because we aim to determine if regular long-term participation leads to different levels of physical activity compared to non-regular participation. Another hypothesis is that finishing the initial 12-session programme is the most powerful predictor for a high level of MVPA. Thus, the sample size calculation is based on between-group differences in MVPA.

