### Logic model

To plan the evaluation, a logic model has been developed. The model is based on the assumption that regular physical activity has a positive impact on health for those who were inactive. [19]. This long-term outcome is shown on the right-hand side of Fig. 1. In the second column from the right, we indicate the expected interim goal of the programme, i.e. participants of the intervention group who received the starter package visit the regional standardised exercise programmes after they return home. The key mechanisms (or psychological mediators) that if enhanced are likely to lead to increased attendance of the exercise programmes are shown in the second column from the left. Finally, in the far left column of Fig. 1, the activities which will take place during the residential stay are listed.

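### The only effect question compares people who choose to attend with those who do not, while the sample size and ANCOVA compare intervention with control; the attendance sub-groups also cannot identify long-term participation

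*Protocol article*

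**What the plan says.** Study objectives (Protocol article) lists two research questions. The first counts uptake. The second is the only question about an effect: "Are those who participate in the exercise programmes more likely to increase their physical activity behaviour than those who do not participate". The Background gives the project aim as the same contrast, that "people who participate in the regional exercise programmes will be more likely to increase their health-enhancing physical activity than those who do not participate".

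Analysis of sub-groups adds a split made after the event: "At the 12-months follow-up, the intervention group will be divided into sub-groups for further analysis". The cut points are 75% and 25% of the 12 sessions. The stated purpose is causal: "we aim to determine if regular long-term participation leads to different levels of physical activity compared to non-regular participation". A further statement reads: "Another hypothesis is that finishing the initial 12-session programme is the most powerful predictor for a high level of MVPA". The section then presents the between-group sample size as following from this.

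Attendance is optional. Participants receive "a voucher for 12 regional, standardised, sports club based exercise sessions which can be attended immediately after the stay". The Logic model section describes what is thought to drive it: "The key mechanisms (or psychological mediators) that if enhanced are likely to lead to increased attendance of the exercise programmes". The Measurements section lists motivation, self-efficacy and social support among these mediators.

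The other sections point to a different comparison. Sample size calculation uses a 44.5 min difference between intervention and control groups. Statistical analyses specifies an ANCOVA between those groups, adjusted for baseline values.

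**The concern.** Two quantities are in play: the difference between attenders and non-attenders, and the difference between residents of intervention and control communities. The article words its effect question as the first, and sizes and analyses the study for the second. It never says which one answers the question.

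The first is open to self-selection. People who are more motivated are plausibly both more likely to use the voucher and more likely to become active without it. The article itself names motivation as a driver of attendance, yet the only adjustment it states is for baseline values. Its limitations mention that non-attenders may become active on their own, but not that attenders select themselves. If the attender contrast is reported as the answer to question 2, some or all of a favourable difference may reflect who attended and not what the programme did.

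A second, independent defect concerns the sub-group variable. It is meant to capture regular long-term participation but counts only the free sessions.

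**Working it through.** **Plan's own figure.** Inputs from Sample size calculation: difference 44.5 (84.1 − 39.6), SD 72.2, two-sided 0.05, power 80%. Standardised difference: 44.5 / 72.2 = 0.616. Normal approximation: n = 2 × (1.960 + 0.842)² / 0.616² = 41.3, so 42 per group. The t-test version gives 42.3, so 43. The stated 42 is reproduced, and it belongs to intervention versus control, not to attenders versus non-attenders.

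**Size of the selection gap (illustration).** Suppose the programme does nothing. Let r be the correlation between readiness to attend and the change in MVPA a person would show anyway, and p the share attending. The article gives neither; both are assumptions. The expected gap is r × 72.2 × φ(c) / [p(1 − p)], where c is the normal quantile at 1 − p. For p = 0.5, φ(0) / 0.25 = 0.399 / 0.25 = 1.596, so the gap is r × 115.2.

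| r | Gap, p = 0.5 | Share of 44.5 | Gap, p = 0.3 or 0.7 | Chance of a significant positive t-test, 48 people |
|---|---|---|---|---|
| 0 | 0 | 0% | 0 | 2–3% |
| 0.1 | 11.5 | 26% | 12.0 | 7–8% |
| 0.2 | 23.0 | 52% | 23.9 | 18–19% |
| 0.3 | 34.6 | 78% | 35.9 | 34–39% |
| 0.4 | 46.1 | 104% | 47.8 | 56–62% |

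The last column comes from 4,000 simulated trials per setting, over p = 0.3, 0.5 and 0.7. With 97 people in the intervention group it becomes 31–35% at r = 0.2 and 62–66% at r = 0.3.

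If the non-participants were taken to be the controls, the attending side would still be selected. The gap is then r × 72.2 × φ(c) / p: at p = 0.5, 5.8, 11.5 and 17.3 min for r = 0.1, 0.2 and 0.3.

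**Sub-group variable.** The Intervention section schedules two sessions per week, so 12 sessions take 12 / 2 = 6 weeks. The top category needs 75% × 12 = 9 sessions, or 4.5 weeks. Someone who stops after the free sessions and someone who continues as a paying member for the rest of the year both fall into sub-group I.

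**Sub-group power.** Assume equal thirds and a two-sample t-test for 44.5 min. With 48 per arm (Sample size calculation), groups of 16 give 39% power, and the difference detectable at 80% power is 74 min. With 194 in total (Eligibility and recruitment), 97 per arm gives groups of about 32, 68% power and a detectable difference of about 51 min. The two totals do not agree (2 × 48 = 96), so both are shown.

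**Cost of the allocated comparison.** If only attenders gain 44.5 min, the group difference is 44.5 × p: 31.2, 22.3 or 13.4 min at p = 0.7, 0.5 or 0.3. t-test power with 48 per group is 55%, 32% or 15%, against 85% if everyone attends.

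**The case against.** The strongest reply is that the right comparison is already there. The abstract describes a two-group study, allocation is by community, and both the sample size and the baseline-adjusted ANCOVA are for intervention versus control. The sub-groups are labelled as further analysis, and calling something a predictor is not in itself a causal claim. Analysis sets and sub-group covariates may be in an analysis plan that is not shown. This stands in part: a reader might infer that the study has no comparison free of selection on attendance, and that would be wrong. The fault is that the stated question and aim do not match the planned comparison, and that the sub-group purpose is worded causally.

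A reader might also infer that a positive answer is bound to appear even if the programme does nothing. The documents do not support that. The expected gap is positive only if r is positive, r and the attendance share are unknown, and at r = 0.1 to 0.3 most simulated trials with 48 people were not significant. The article's own remark that non-attenders may become active independently also works towards narrowing the gap.

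Nor do the documents say that the control communities were chosen to remove self-selection. The reason given under Eligibility and recruitment is that three of the intervention communities are small. Allocation is not randomised, so the allocated comparison has its own limits, but that is no reason to add selection on attendance.

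Finally, the process evaluation already counts sessions attended and people who start the long-term programme. The information for a better definition is therefore planned, but the sub-group definition does not use it.

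**Conclusion.** The point holds as a mismatch that should be corrected. Question 2 and the project aim are worded as a contrast between self-selected attenders and non-attenders, and the sub-group section asks what attendance leads to, while the sample size and ANCOVA are for intervention versus control. Followed as written, the only effect question would be answered by a confounded contrast.

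The size of the bias cannot be determined from the documents. The 12, 23 and 35 min figures illustrate it under assumed correlations, half attending, the article's SD of 72.2 and no programme effect. They show that modest selection could produce a gap that is a material part of the 44.5 min target; they do not predict a false positive.

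The sub-group defect rests on no such assumption: a count limited to the 12 voucher sessions cannot identify long-term participation. Sub-group comparisons would also be weak, with 39% to 68% power under equal thirds, depending on which of the two stated totals applies.

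**What to change.** 1. Reword question 2, and the matching aim in the Background, as the baseline-adjusted difference in MVPA between residents of the intervention and control communities, all included people analysed as allocated regardless of attendance. State that the ANCOVA already described answers it.
2. Report the attendance sub-groups as descriptive associations, adjusted for baseline MVPA, motivation and self-efficacy, and drop the causal wording. Adjustment reduces the selection bias but cannot be relied on to remove it.
3. Define long-term participation by all sessions attended over the 12 months, including the paid phase.
4. A complier-average estimate (arm difference divided by attendance proportion) is optional and secondary. It must state two assumptions: that the communities are comparable, and that the offer affects MVPA only through attendance. The second is open to doubt because the arms also receive different information, a starter package against a brochure.

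Items 1 and 2 need text changes and use data already planned. Item 3 needs attendance records to cover the paid phase. The real cost is dilution of the allocated-group effect by non-attendance, with the loss of power shown in the working. The expected attendance should therefore be stated and the sample size checked against it, once the totals of 96 and 194 are reconciled.
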